**Figure 1 F1:**
[figure not shown]
CONSORT diagram illustrating the study phases. T1: baseline; T2: Post-intervention; T3: 6-Month follow-up; MBCT-C: Mindfulness-based Cognitive Therapy for Children; MAAS-C-: Mindful Attention Awareness Scale- Adolescents; STAI-CH: State-Trait Anxiety Inventory for Children; ERC: Emotion regulation checklist; ACS-C: Attentional Control Scale for Children; MPSQ: Mindfulness Program Satisfaction Questioner (MPSQ).

### Sample size

According to Thibault & Pedder (55) and Treves et al. (56), the required sample size for this study to achieve sufficient statistical power was determined using G*Power software (57). In this calculation, we used *a priori* power analysis with the following parameters: significance level *α* = .05; effect size = .5 (58); power (1-*β*).95; with two groups, corresponding to the study design. A minimum of 64 participants was estimated to detect hypothesized effects reliably. Recognizing the possibility of participant attrition, we incorporated a buffer to protect the power of the study. Specifically, we estimated a dropout rate of 20%, increasing the sample by an additional 14 participants (calculated as 20% of 64, rounded). This adjustment resulted in a total sample size of 77 (rounded to 80) participants. However, we acknowledge that this sample size limits our ability to detect smaller effect sizes. We have adjusted our expectations accordingly, focusing on larger effects as suggested by prior research (e.g., Goldberg et al. (59), for mindfulness interventions on stress.

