The development of effective psychotherapies aimed at addressing emotional problems in children has made significant progress (14, 16, 39). Mindfulness-based interventions, in particular, are of growing interest. Mindfulness is an approach to life experiences that emphasizes attention to the present moment and with an attitude of non-judgment (40). Mindfulness, cultivated through meditation, involves bringing awareness to one's thoughts, emotions, and bodily sensations without engaging reactively to them (41, 42). Mindfulness-based interventions, which have been influential in evolving the third wave of cognitive-behavioral therapies, were developed initially for adults, but have now been adapted for children (43).

Mindfulness-based cognitive therapy (MBCT) was developed for relapse prevention in adult patients with recurrent depressive episodes (44, 45), and was later adapted for other problems and populations (46). One of these adaptations, MBCT-C, employs the same methodology as the adult program and shares analogous goals and objectives; however, it has been specifically tailored for children, which includes modifications to the duration of the sessions and the incorporation of child-friendly language and content (47). MBCT-C may be an effective intervention in mitigating emotional difficulties among children and adolescents (48, 49). A study conducted to investigate the effectiveness of MBCT-C on children and adolescents suffering from anxiety disorders who were at risk of bipolar disorder revealed that MBCT-C is effective in reducing clinical symptoms. Additionally, improvements in mindfulness were associated with improvements in anxiety and emotion regulation (50). The effectiveness of MBCT-C has been repeated in other clinical samples, including children with math anxieties (51), cancer (39), and internalizing disorders (52). The results of a meta-analysis, which compiled results from 3,977 child and adolescent mindfulness-based interventions, showed that the effect size of these interventions is small to moderate, and that the effectiveness appears to vary based on two factors: the type of facilitator and the characteristics of the program (53). Therefore, mindfulness-based interventions for children and adolescents in both clinical and non-clinical populations need further evaluation.

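### The stated inputs (alpha .05, effect size .5, two groups) do not give 95% power with 64 participants on the natural reading; at d = 0.5, 64 analysed gives about 50%

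*Protocol article*

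**What the plan says.** The Sample size section of the protocol reports an a priori G*Power calculation with "significance level *α* = .05; effect size = .5 (58") and "power (1-*β*).95; with two groups, corresponding to the study design". Its result is that "A minimum of 64 participants was estimated to detect hypothesized effects reliably".

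The section then allows for 20% dropout by adding 14 children, and "This adjustment resulted in a total sample size of 77 (rounded to 80) participants". The Procedure section confirms 80 in total: four cohorts of 20, with 10 per group in each. So 64 is the number expected across both arms together.

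The section does not name the test, the effect-size metric, the sidedness, the number of measurements or a within-child correlation. The Introduction cites a meta-analysis of mindfulness programmes in children and adolescents that "showed that the effect size of these interventions is small to moderate". The Statistical strategy section plans a mixed model with group, time and their interaction over three assessments.

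**The concern.** For a standardised mean difference of 0.5 between two groups, 64 in total is far too few for 95% power, so the stated inputs and the stated result do not appear to belong together. This calculation is the only numerical justification for the trial's size.

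The stake is how the result will be read. The comparator is an active programme whose sessions also include breathing exercises and emotional management, so a non-significant difference is quite possible. A reader told that power was 95% would take such a result as strong evidence against an effect of the planned size. If the true power is near one half, it would be no such evidence.

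**Working it through.** **Inputs.** Alpha .05, effect size .5, power .95, two groups, minimum total 64, final total 80 (Sample size); 1:1 allocation (Recruitment and randomization procedures). Assumptions, because the document is silent: .5 is Cohen's d, and the test is two-sided.

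**Trying to reproduce 64.** For two equal groups with total N, the noncentrality is δ = d·√(N/4), on N − 2 degrees of freedom. The normal approximation for 95% power is n per group = 2(1.960 + 1.645)²/0.5² = 2 × 12.996/0.25 ≈ 104. The exact noncentral t gives 105 per group, 210 in total. One-sided, it is 88 per group, 176 in total. Neither is 64.

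**Power at the relevant totals (two-sided, d = 0.5).**

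| Total N | δ = 0.5·√(N/4) | Power |
|---|---|---|
| 64 | 0.5 × 4.000 = 2.00 | 50.4% |
| 80 | 0.5 × 4.472 = 2.24 | 59.8% |
| 128 (64 per group) | 0.5 × 5.657 = 2.83 | 80.1% |
| 210 | 0.5 × 7.246 = 3.62 | 95.0% |

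One-sided power with 64 in total is 63.1%. The detectable d with 64 analysed is 0.71 at 80% power and 0.92 at 95%. With 80 analysed it is 0.63 and 0.82.

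**Baseline adjustment.** With baseline-outcome correlation r, the effective effect is d/√(1 − r²). With 64 analysed at one time point:

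| Assumed r | 0.5/√(1 − r²) | Power, N = 64 | N for 95% |
|---|---|---|---|
| .3 | 0.524 | 54% | 192 |
| .5 | 0.577 | 62% | 158 |
| .7 | 0.700 | 79% | 108 |

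Power reaches 95% with 64 only at r of about .84, where the effective effect is 0.92.

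**Reading .5 as Cohen's f.** In two groups d = 2f, so f = .5 means d = 1.0. A one-way ANOVA then needs 54 in total, and 64 would give 97.6%. Between-group or interaction repeated-measures F tests whose noncentrality includes the correlation, with f = .5, two or three measurements and correlations from 0 to .7, need between 10 and 48.

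**Set-ups that do reach 64.** Take a group-by-time interaction with three measurements, on 2 and 2(N − 2) degrees of freedom.
- With f = .5 and noncentrality λ = f²N = 0.25N, power is 95.2% at N = 64 and 94.6% at N = 62, so the minimum balanced total is 64. A multivariate version needs 65 to 66.
- With f = .25 and correlation .25, λ = f²·3N/(1 − .25) = 0.0625 × 3N/0.75 = 0.25N, which is the same λ and again gives 64. The total moves quickly with the correlation: 84 at 0, 60 at .3, 44 at .5.

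**Dropout line.** 20% of 64 is 12.8, or 13, not 14. The stated 77 matches 64 × 1.2 = 76.8, whereas 64 + 14 = 78. Allowing properly for 20% loss gives 64/0.8 = 80, so the final total does cover 20% loss from 64.

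**The case against.** The best defence is that the calculation was meant for the planned repeated-measures analysis. The section says its inputs correspond to the study design, three assessments are stated elsewhere, and group-by-time is a planned fixed effect. An interaction test with f = .5 and λ = f²N keeps alpha .05, .5, .95 and two groups, and returns exactly 64 as a total. A condensed article may also leave the test family and metric to a fuller document.

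Part of this stands. A reader might infer that no calculation can yield 64; that is not so. But the set-ups that yield it need a noncentrality convention or a correlation that the section does not give, and one of them replaces .5 by .25. Nor do they describe a half-SD difference between groups. If the groups are equal at baseline and differ by 0.5 SD at both later assessments, the interaction effects are ±(−1/6, 1/12, 1/12), and f = √[(1/36 + 1/144 + 1/144)/3] = √(1/72) ≈ 0.12, well below .25 or .5. And f = .5 in a simple two-group test is d = 1.0, which sits badly with the effects described in the Introduction.

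A reader might also infer that the cause is known: 64 is the per-group size for 80% power at d = 0.5, reported as a total at 95%. The match is exact and suggestive, but it would need two slips at once, and the document does not show how the number arose.

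Nor is 50% the power of the planned mixed model. It belongs to an unadjusted contrast at one time point. Averaging the two later assessments with baseline adjustment, under equal correlations among all three, would give about 75%, 80% or 91% with 64 at correlations of .3, .5 or .7. That is a different contrast, and it still falls short of 95% at those correlations.

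Finally, the authors concede that the sample limits detection of smaller effects, say that they focus on larger ones, and list sample size as a limitation in the Discussion. That is fair, but it does not withdraw the claim of 95% power at .5.

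**Conclusion.** The point holds in this form: the stated inputs do not yield 64 on the natural reading, and the claimed power is not supported by what the section gives. At d = 0.5, two-sided, 95% power needs 210 in total. With 64 analysed, power at one time point is about 50% unadjusted and about 54% to 79% with baseline adjustment (correlation .3 to .7). With all 80 it is about 60% unadjusted.

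This rests on reading .5 as Cohen's d, which is an assumption, though the usual one for two groups and in keeping with the effects cited in the Introduction. The arithmetic given that reading is certain. The origin of 64 is not established, and the power of the planned mixed model cannot be computed from what the section states. The dropout slip is real but harmless to the final 80.

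**What to change.** Keep 80, and rewrite the Sample size section as follows.

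1. State the test, the effect-size metric, the sidedness, the number of measurements and the assumed within-child correlation.
2. Replace .95, and the word *reliably*, with the power that this calculation gives. For a contrast of d = 0.5 at one time point with 64 analysed, that is about 50% unadjusted, or about 54% to 79% with baseline adjustment (assumed correlation .3 to .7). The detectable effect at 80% power, unadjusted, is d = 0.71.
3. Say that a non-significant result will be interpreted from its confidence interval.
4. Correct the dropout line: 20% of 64 is 13, and 64/0.8 = 80.

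The cost is a change of wording and a less favourable stated power. No extra participants are needed.

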### Recruitment and randomization procedures

In this study, our sampling framework encompasses four schools (two female-only and two male-only institutions) randomly selected from diverse districts across Tehran to ensure appropriate population representation. The target population comprises all middle school students in Tehran who, according to Iran's educational system, attend gender-segregated schools.

The necessary research permits will be obtained from Tehran's Education Department through the university's Research Vice-Chancellor's office. Group intervention sessions will be conducted after regular school hours in the counseling rooms of the participating schools, providing a quiet and appropriate environment for group therapeutic activities. This approach facilitates student access to the program while avoiding interference with their academic schedules.

Furthermore, school counselors will explain the research and introduce interested parents and students to the research team. Should these recruitment techniques be insufficient to obtain the desired sample size within a reasonable time, we will extend recruitment to additional schools within the Tehran education district.

Potential participants who contact the research assessment team will undergo an in-person screening to determine their eligibility. Inclusion criteria include: (a) primary school students, (b) age between 8 and 12 years old, (c) living in Tehran, and (d) ability to speak Persian. Exclusion criteria comprise (a) reporting an acute physical illness, (c) receiving psychotropic medications, and (e) receiving concurrent psychotherapy. Children who meet the criteria for this study and agree to participate will be enrolled with the consent of a parent or caregiver. Once the desired sample size is enrolled, participants will be randomized to the MBCT-C or LST group using online random allocation software (https://miniwebtool.com/de/number-randomizer/). The allocation will be made in a 1:1 ratio, ensuring equal representation of participants in each group.

### Procedure

Participants will be recruited from public elementary schools in Tehran. We will employ a staged recruitment approach, enrolling four cohorts of 20 children each (80 total). As each cohort of 20 children is recruited, they will be randomly assigned to either intervention or control groups (10 per group), and the 12-week programs will begin. While the first cohort undergoes treatment, recruitment for subsequent cohorts will continue.

Interested children will participate in a brief eligibility screening. Eligible students and their parents will receive comprehensive information about the study. Participation requires written informed consent from a parent or guardian and verbal assent from the child. Participants assigned to the intervention group will attend weekly 90-minute MBCT-C sessions for 12 weeks. The control group will participate in a 12-week LST program. Each program will be facilitated by separate instructors trained and invested in their respective models to prevent potential bias.

Protocol adherence will be monitored using the MBCT-C adherence scale and an equivalent measure for LST. A trained supervisor will review recorded sessions and provide feedback to facilitators to ensure standardized protocol implementation. Participants will complete the T2 assessment battery at the end of the intervention and the T3 follow-up assessment six months later. The Client Satisfaction Questionnaire (CSQ-8) will measure participant satisfaction with both programs.

### Mindfulness-based cognitive-behavioral therapy-children (MBCT-C)

MBCT-C (47) is a manualized 12-week treatment protocol that focuses on addressing attentional problems and anxiety-spectrum disorders in children. This protocol is designed for children between 8 and 12 years old and includes a variety of meditation and mindfulness techniques to improve cognitive, emotional, and physical awareness.

MBCT-C consists of three sequential steps to improve mindfulness. In the first phase (Sessions 1–3), in addition to preparing participants to overcome the obstacles ahead and how to do the tasks, exercises for conscious breathing, body awareness, and mindfulness will be presented. The second step of MBCT-C (sessions 4–10), which constitutes the principal portion of interventions, is aimed at thoughts, emotional experiences, and physical sensations in a more adept manner ways. Participants will engage in exercises designed to enhance mindfulness in each of their five senses. Additionally, based on informed and non-judgmental observations, they will examine various alternative ways of responding to challenging thoughts, emotions, and external events. In the final stage of the program (sessions 11 and 12), participants are taught to integrate mindfulness practices into their daily routines. Participants will discuss maintaining a daily practice of mindfulness and discuss benefits that may have been experienced during the program. Three months after the end of the program, each participant will receive a letter written by themselves in session 11 to motivate themselves to continue a consistent daily practice. At each session, written session summaries, homework assignments, poems, or stories related to that session, are provided to the participants (Table 1).

**Table 1 T1:** The session-to-session content of the MBCT-C protocol [Semple and Lee, (47)].

Sessions	Content of session	Assignments
Session 1 Being on automatic pilot	• The main concepts and structure of sessions. • Differences between habitual life and mindful life.	• Awareness of thoughts and emotions • Awareness of automatic behaviors • Mindful breathing
Session 2 Being Mindful	• Paying attention to the present moment. • Increasing the duration of being mindful. • Dealing with internal obstacles (including thoughts and emotions). • Differences in reactions when awareness is incomplete compared to when there is a mindful state.	• Practicing breathing exercises and mindful eating meditation throughout the week
Session 3 Who Am I?	• Considering thoughts as possibilities rather than facts. • Being aware of the presence of thoughts. • Improving reactions with mindfulness.	• Mindful breathing • Mindfulness of the body
Session 4 A Taste of Mindfulness	• Considering other aspects of the present experience. • Find new ways to experience. • Exploring more awareness, compassion, and capacity for challenging situations.	• Three-minute breathing space • Mindful yoga movements • Tasting fruits
Session 5 Music to Our Ears	• Engaging in attentive listening to voices and sounds. • Identifying psychological obstacles that hinder the ability to maintain attention.	• Three-minute breathing space • Mindfulness of the body • Mindful listening
Session 6 Sound Expressions	• Exploring the role of thoughts and feelings on vocal expression. • Increasing awareness of finding more choices in response to experiences.	• Three-minute breathing space • Mindfulness of the body • Unpleasant sounds
Session 7 Practice Looking	• Non-judgmental attention to what we see. • Mindful observation exercises.	• Three-minute breathing space • Seeing the little details
Session 8 Strengthening the Muscle of Attention	• Developing awareness of both external and internal perceptions. • Disabling the autopilot mode and cultivating a state of mindful awareness. • Avoiding blame and cultivating compassion during meditations.	• Three-minute breathing space • Choosing to be aware • Seeing five new things
Session 9 Touching the World	• Bringing awareness to everyday experience. • Taking notes about experiences.	• Three-minute breathing space • Mindfulness of the body • Mindful Touching
Session 10 What the Nose Knows	• Practicing mindful smelling. • Determining how to react to unpredictable and uncontrollable events.	• Three-minute breathing space • Mindful Yoga movements • Mindful smelling
Session 11 Life Is Not Rehearsal	• Accepting the presence of judgmental thoughts without engaging. • Cultivating acceptance and expanding greater compassion.	• Three-minute breathing space • Letter to myself
Session 12 Living with Presence, Compassion, and Awareness	• Involved in practical strategies for building a daily routine based on mindfulness.	• Letter from therapist to child • Daily practice calendar

### Life skills training (LST)

LST is a comprehensive 12-week group program, developed by GJ Botvin and KW Griffin (60) developed to help participants practice ten essential life skills. The skills covered include self-awareness, empathy, interpersonal communication, coping with stress, decision-making, problem-solving, emotional management, creative thinking, critical thinking, and effective communication. Like the MBCT-C program, LST incorporates practice during sessions and assigns homework. Based on the sessions' practices, upon learning each skill, participants reflect on a recent challenging situation in their lives and utilize the skills acquired to reevaluate that situation, developing appropriate responses. During each session, a facilator elucidates the skills to the participants and facilitate their learning through constructive feedback. As part of their homework, participants are encouraged to effectively implement the skills they have acquired to manage various situations encountered throughout the week. In each session, the homework from the previous session is collectively reviewed in a shared space (Table 2). Two distinct therapists will facilitate the LST and MBCT-C group sessions. We have selected therapists with specialized training and experience in their respective programs. This approach mitigates the risk of bias if a single individual were to conduct both programs, particularly given varying levels of expertise or personal preference.

**Table 2 T2:** Introduction to the life skills training program.

Sessions	Main contents	Assignments
Session 1 Introduction	• Warming up • Introduction to the program • Fostering Engagement and Mutual Respect • Guiding participants on doing homework exercises	• None
Session 2 Self-Awareness	• Promoting self-reflection on values, beliefs, and traits • Recognizing personal strength points • Identifying personal weaknesses • Expressing their emotions • Encouraging self-reflection, self-acceptance, and personal growth	• Self-monitoring
Session 3 Empathy	• Identify and effectively address the emotions of people • Practicing active listening, non-judgmental language	• Documenting their experiences with others
Session 4 Interpersonal Communication	• Active listening • Clear expression of ideas • Respectful dialoguing	• Active Listening Exercise • Perspective-Taking Exercise
Session 5 Effective Relationship	• Creating meaningful connections • Doing joint activities • Attention to the interests of friends and relatives • Resolve conflicts constructively • Strengthening mutual understanding	• Monitoring Previous skills • Practicing improving current relationships
Session 6 Coping Stress	• Breathing exercises • Adopting healthier habits • Engaging in physical activity	• Breathing exercises • Building good habits • Doing exercise
Session 7 Problem Solving	• Identifying the problem • Brainstorming • Evaluation of the solutions • Implementing the most optimal one • Evaluating the consequences	• Practicing on daily problems and documenting them
Session 8 Decision-Making	• Evaluating costs and benefits • Searching for Information and Insights • Collaborative decision-making processes • Mitigating risks and uncertainties • Confident and responsible decision-making	• Documenting decision-making for daily situations
Session 9 Creative Thinking	• Cultivating an innovative mindset • Exploring Unconventional Solutions • Embracing imagination and divergent thinking • Overcoming mental blocks and biases	• Brainstorming, mind mapping, and lateral thinking regarding an interesting issue
Session 10 Critical Thinking	• Logical Inquiry • Evaluating Information with Objectivity • Identifying Assumptions and Biases • Drawing Well-Reasoned Conclusions	• Evaluating the source's credibility, bias, and potential motives in a newspaper
Session 11 Emotional Management	• Implementing progressive muscle relaxation • Practicing cognitive reframing • Identifying emotional triggers • Substituting avoidance with experiencing.	• Identifying emotional triggers and using a strategy to expose them effectively
Session 12 Maintain achievements	• Reviewing and discussing the previous sessions • Implementing the skills in everyday life • Continuing monitoring • Documenting worksheets and diaries	• None

